### Blinding

For obvious reasons, this study cannot be blinded, either on the patient’s side (receiving or not receiving headphones, and listening or not listening to music during NIV sessions) or the caregiver’s side (helping the patient to choose the music and to adjust the headphones and the blinding mask). However, the evaluation of the primary endpoint is performed blindly from the treatment group according to the prospective randomized open blinded endpoint (PROBE) method [22]. Indeed, the primary endpoint is respiratory comfort after the 30 minutes of the first NIV session after randomization; this endpoint is assessed by an independent person who did not participate in the initiation of the NIV session and has no knowledge of the actual treatment received during the session. The organization of our ICUs allows requiring a blinded evaluator such as a nurse or a nursing assistant from another unit. The patient is told to not give any clue about the randomization arm during the evaluation. This same investigator will conduct assessments of the following NIV sessions; as far as possible, his/her independence with regard to the randomization group will be maintained in subsequent NIV sessions.

### Study interventions

The study protocol and the three randomization arms are summarized on Fig. 1.

**Fig. 1 Fig1:**
[figure not shown]
Study protocol and randomization arms. Pressure support is progressively increased in order to obtain a respiratory rate between 15 and 25 cycles per minute, an exhaled tidal volume of 6–10 ml/kg of predicted body weight, and the disappearance of signs of respiratory distress. Positive end expiratory pressure is set 2–6 cm H_2_O above pressure support and adjusted according to patient’s tolerance. FiO_2_ is set to obtain a minimal pulse oximetry of 92 %. *NIV* non-invasive ventilation, *PS* pressure support, *RR* respiratory rate, *Vte* exhaled tidal volume, *PBW* predicted body weight, *FiO*
_*2*_ fraction of inspired oxygen, *SpO*
_*2*_ peripheral capillary oxygen saturation, *EPAP* expiratory positive airway pressure, *ICU* intensive care unit

#### NIV conduction in all three groups

NIV is initiated according to standards of care and in line with each participating ICU’s practices. The detailed NIV protocol is given in Additional file 1. Briefly, masks are chosen according to the patient's morphology, and the physician in charge, along with the nurse and the nursing assistant, initiates the first session.Ventilator settings

Initial ventilator settings are chosen to maximize the patient's tolerance and minimize air leaks, in order to obtain a respiratory rate between 15 and 25 cycles per minute, an exhaled tidal volume of 6–10 ml/kg of predicted body weight, and the disappearance of signs of respiratory distress. FiO_2_ is set to obtain a minimal pulse oximetry of 92 %. The duration of NIV sessions is left to the discretion of the physician in charge, based on the patient’s needs.Subsequent NIV sessions

The subsequent NIV sessions are conducted by the nurse and nursing assistant according to a prespecified timeline: the physician in charge prescribes the length of NIV sessions and the number per day.Patient monitoring during NIV sessions

All patients undergo careful monitoring to detect and treat any complications related to ARF or NIV. Criteria for intubation are those in use in the participating ICUs [23].

#### Control group: “NIV only”

In this group, NIV is conducted as detailed above. Usually, the nurse and the nursing assistant provide psychological support and relaxation care to help the patient cope with NIV discomfort.

#### “Sensory deprivation” group

In this group, NIV is conducted similarly as for the former group but with the addition of sensory deprivation. Sensory deprivation consists of isolating participants from the noise and lights of the ICU:An insulating around-ear headphone (BOSE AE2®, the same as that used in the latter intervention arm) is placed on the patients’ ears by the unblinded caregivers, once the NIV mask has been fitted and the ventilator settings optimized.Applying a sleeping mask conceals the eyes. If the patient does not tolerate being blindfolded (e.g., due to claustrophobia), alternative solutions are suggested to the patient (such as closing his eyes or using a personal scarf) to make him feel at ease. The purpose of the visual deprivation is to avoid the patient being disrupted from the relaxation process because of visual distractions.

The headphones and mask will be left in place for 30 minutes. Data regarding tolerance and possible rejection of sensory deprivation will be collected.

After inclusion, all NIV sessions are conducted as detailed above until NIV discontinuation, day 28, or ICU discharge.

#### “Musical intervention" group

NIV is conducted as detailed above, including visual isolation. The musical intervention is initiated starting from the first NIV session that follows randomization.Once the NIV mask has been fitted and the ventilator settings optimized, the trained nurse or nursing assistant sets up the headphones (BOSE AE2®), presents the tablet interface (Samsung Galaxy®), and shows the patient how to handle it.The patient’s musical tastes are determined by a caregiver-administered questionnaire, either to the patient or to her relatives if the patient is unable to express her musical choices (moderate impairment of consciousness). The patient therefore chooses the musical program, with MUSIC CARE^©^ software [19, 24, 25], according to her musical preferences, sets the volume level, and runs the musical session.The musical intervention session lasts 30 minutes and contains two phases, called an L-type sequence (Fig. 2) [24]; the downswing phase is achieved by reducing the musical rhythms starting at high tempos and a high number of instruments, gradually leading to slower tempos and reducing the number of instruments, the frequencies, and the volume. Then the patient is moved through a maximum relaxation phase with a slow-paced rhythm and reduced orchestras, resulting in maximum relaxation (bottom of the “L”).If the patient asks for more than 30 minutes of musical intervention, the session is extended towards a ”U-type” [25].

**Fig. 2 Fig2:**
[figure not shown]
Musical intervention with the L-type sequence [24]. This sequence begins with a downswing phase, achieved by reducing the musical rhythms and the number of instruments, the frequencies, and the volume, and a maximum relaxation phase with a slow-paced rhythm and reduced orchestras (bottom of the L). *bpm* beats per minute

After inclusion until NIV discontinuation, day 28, or ICU discharge, all NIV sessions are performed according to this mode.

## Data collection and follow-up

Collected data at each time are summarized in the SPIRIT schedule of events shown in Table 1.

**Table 1 Tab1:** Summary of collected data at each time point according to SPIRIT 2013 guidelines

			Study period							
	Enrollment	Allocation	Post-allocation — at each NIV session						NIV discontinuation, ICU discharge or day 28	Close-out Day 90
Time point			*t* _1_ beginning of NIV session	*t* _2_(*t* _1_ + 5 min)	*t* _3_(*t* _1_ + 30 min)	*t* _4_(*t* _1_ + 1 h)	*t* _*x*_ ^a^	End of each NIV session		
Enrollment:										
Eligibility screen	X									
Informed consent	X									
Allocation		X								
Interventions:										
Musical intervention										
Sensory deprivation										
Control group										
Assessments:										
*Baseline variables:* Demographic data and medical history, SAPS III, SOFA	X									
*Outcome variables:* Respiratory comfort, RASS			X	X	X	X	X	X		X
Respiratory and hemodynamic parameters		X	X	X	X	X	X	X		
*Ongoing therapies:* Catecholamine infusion, need for ETI, attempts to pull out NIV mask, headphones or sensory isolation, need for physical contention, sedative or anxiolytic treatments, NIV complication		X						X		
Health-related quality of life (HADS and SF-36 scores)		X								X
Length of ICU and hospital stay										X
Vital status, NIV satisfaction, comfort and associated trauma, IES-R for NIV									X	X
Decision to withhold life-sustaining therapies									X	

*NIV* non-invasive ventilation, *ETI* endotracheal intubation, *HADS* Hospital Anxiety and Depression Scale [28], *IES-R* Impact of Event Scale - Revised [31], *RASS* Richmond Agitation-Sedation Scale [30], *SAPS III* Simplified Acute Physiological Score III [26], *SF-36* Short Form-36 [29], *SOFA* Sequential Organ Failure Assessment [27]

^a^
*t*
_*x*_ stands for *t*
_1_ + 2, 3, 4, 6, 8, 12, 16, 20, 24 hours depending on the length of each NIV session

### At day 1 (baseline)

Demographic data and medical history, including the current clinical history with the reason for ICU admission, Simplified Acute Physiology Score III severity score [26], and Sequential Organ Failure Assessment score [27], are collected.

Treatments including NIV (and its settings), fluid therapy, catecholamine infusion, and endotracheal intubation are recorded. Laboratory tests include serum (and urine if diuresis is present) electrolyte levels determination, serum glucose level, urea and creatinine concentration, and arterial blood gas determination. Respiratory and hemodynamic parameters before the beginning of the NIV session (respiratory rate, exhaled tidal volume, PaO_2_/FiO_2_ ratio, heart rate, arterial pressure) are collected.

The research team administers to the patient, or to a proxy if the patient is not able to answer, the baseline Hospital Anxiety and Depression Scale (HADS) questionnaire [28] and Short Form-36 (SF-36) [29] in order to determine the baseline health-related quality of life.

### At each NIV session, until NIV discontinuation or day 28

The prescribed duration of the NIV session is recorded. Prior to each NIV session, immediately after NIV is correctly set (5 minutes), at 30 minutes, and at 1, 2, 3, 4, 6, 8, 12, 16, 20, 24 hours depending on the length of each NIV session, and at the end of the session, the following data are collected:Respiratory comfort assessed by a blinded evaluator (nurse from another unit) with the use of a numeric visual scale [14]The same respiratory and hemodynamic parameters as the initial onesAgitation assessed by Richmond Agitation-Sedation Scale [30].

For each NIV session, the need for physical contention or sedative or anxiolytic treatments is assessed and recorded. The tolerance of sensory isolation is recorded, as well as attempts to pull off the NIV mask or headphones. At the end of each session, data for its exact duration, the reason of its premature ending if appropriate, and the need for endotracheal intubation are collected. Furthermore, arterial blood gases are reported when these tests are performed as clinically indicated. The occurrence of nasal bridge ulcers or irritations is also recorded. For the “musical intervention” group, the type of music chosen and the feeling experienced during the session are recorded.

### At NIV discontinuation, ICU discharge, or day 28

Apart from endotracheal intubation, the need for tracheostomy during the ICU stay and vital status at ICU discharge are recorded. Patients are surveyed for numeric scaling of NIV satisfaction, NIV comfort, and NIV-associated trauma. The Impact of Event Scale - Revised (IES-R) [31] is applied to NIV.

### At day 90

Vital status is regularly updated for each patient until the end of the study. In order to determine the 3-months health-related quality of life, numeric scaling of NIV satisfaction, NIV comfort, and NIV-associated trauma, the IES-R applied to NIV, and the HADS questionnaire [28] and SF-36 [29] are determined and recorded by a blinded-to-randomization group research staff member through a phone survey of patients who are alive.

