### Ethical aspects

The ethics committee of the French Society for Intensive Care Medicine (Commission d’Ethique de la Société de Réanimation de Langue Française approval CE SRLF 14–21) and the competent French authorities (Comité de Protection des Personnes d’Île de France IV, Hôpital Saint-Louis; registration number 2014-A00643-44; date of approval 26 March 2015) approved the study protocol and patient information documents. According to French law on interventional studies, the patient’s (or his next of kin’s) written informed consent is mandatory for inclusion and randomization.

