### Inclusion and exclusion criteria

The inclusion criteria are as follows:Adults (≥18 years of age)For whom the physician in charge considers that NIV is indicatedWith a level of consciousness good enough to benefit from the musical intervention (Glasgow Coma Scale ≥12).

The non-inclusion criteria include:Patients with a classical contraindication to NIVPatients with severe hearing impairmentPatients for whom a decision of withdrawal of life-sustaining therapies has been made, and with an estimated life expectancy of less than 48 hrsPatients included in another trial dealing with an ARF treatment strategy.

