##### Percentage of patients requiring physical restraints or administration of anxiolytics or sedatives during NIV sessions, percentage of intubated patients

These percentages will be compared between groups by the usual tests for comparing proportions.

##### SF-36, HADS scores, IES-R scores, and overall assessment of NIV between inclusion and day 90

The evolution of these scores between baseline and day 90 (difference between the measurement at 3 months and inclusion) will be compared between groups by the usual tests comparing continuous variables.

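### HADS and SF-36 change scores can subtract a proxy's baseline from the patient's own day-90 answer, so part of the reported change is a switch of rater

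*Protocol article*

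**What the plan says.** Four parts of the protocol article bear on this.

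- **Who is enrolled.** Inclusion asks for "a level of consciousness good enough to benefit from the musical intervention (Glasgow Coma Scale ≥12"). The description of the musical intervention arm provides for the music questionnaire to go "to her relatives if the patient is unable to express her musical choices (moderate impairment of consciousness"). Under Ethical aspects, next of kin may give consent.
- **Baseline rater.** The section on day 1 reads: "The research team administers to the patient, or to a proxy if the patient is not able to answer, the baseline Hospital Anxiety and Depression". The instrument meant is HADS, and the SF-36 is handled in the same way.
- **Day-90 rater.** Under At day 90, HADS and SF-36 are obtained "through a phone survey of patients who are alive". A proxy is named at baseline and not here.
- **Analysis.** The paragraph on SF-36, HADS, IES-R and the overall assessment of NIV defines the outcome as the "difference between the measurement at 3 months and inclusion", which "will be compared between groups by the usual tests comparing continuous variables". It has no term for baseline or for who answered.

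**The concern.** HADS asks about feelings that a relative can only infer, and much the same holds for parts of the SF-36. If a relative answers at entry and the patient answers three months later, the difference between the two scores is not a clean within-patient change. The analysis pools such differences with genuine within-patient changes and treats them alike.

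Two things are at stake. The first is interpretation: the Discussion presents anxiety, depression and quality of life at baseline and day 90 as patient-reported outcomes, yet some baselines may not be patient-reported. The second is precision: rater disagreement adds noise to a comparison with at most 33 patients per arm, and fewer once deaths and non-response at day 90 are counted.

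**Working it through.** The plan gives no figure on this point to reproduce. The sample size concerns the primary endpoint, which the participant marks on the scale, and is not affected.

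**1. Does the situation arise?** The baseline text names a proxy for patients who cannot answer, and the musical intervention section expects some enrolled patients to be unable to state their choices. Those two statements settle it. The Glasgow threshold alone would not, since it says nothing about ability to answer a questionnaire.

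**2. What the change score contains.** For a patient with a proxy baseline:

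day-90 (patient) − baseline (proxy) = [day-90 (patient) − baseline (patient)] + [baseline (patient) − baseline (proxy)]

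The first bracket is true change and the second is the rater gap.

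**3. Effect on arm means and on the contrast.** Let q be the share of proxy baselines in an arm and b the mean rater gap. The arm's mean change moves by q × b. The difference between arms A and B moves by b × (qA − qB), which has expectation zero if proxy use is independent of arm.

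**4. Effect on variance.** Work in units of the self-report SD. Let r be the correlation between self-reported baseline and day 90, and e the SD of proxy error, independent of the true score. Without proxies the change score has variance v0 = 2(1 − r). Proxies add q·e² + q(1 − q)·b².

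The article gives none of q, b, e or r. Assumed ranges: q 10–40%, b 0.2–0.5, e = 0.7, r 0.3–0.7.

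| r | q | b | v0 | Added variance | Variance ratio | Shift in arm mean (q × b) |
|---|---|---|---|---|---|---|
| 0.3 | 0.10 | 0.2 | 1.40 | 0.049 + 0.0036 = 0.053 | 1.038 | 0.02 |
| 0.5 | 0.25 | 0.5 | 1.00 | 0.1225 + 0.0469 = 0.169 | 1.169 | 0.125 |
| 0.7 | 0.40 | 0.5 | 0.60 | 0.196 + 0.060 = 0.256 | 1.427 | 0.20 |

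The first and last rows are the extremes of the grid. In terms of precision, 33 patients per arm are worth 33/1.038 = 31.8, 33/1.169 = 28.2 and 33/1.427 = 23.1 respectively.

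**5. Chance imbalance between arms.** Suppose proxy use differs by 15 percentage points between two arms (about 5 of 33). The contrast moves by 0.15 × 0.2 = 0.03 to 0.15 × 0.5 = 0.075 SD. The standard error of the contrast without rater noise is √v0 × √(2/33), which is 1.18 × 0.246 = 0.29 at r = 0.3 and 0.77 × 0.246 = 0.19 at r = 0.7. The shift is therefore about 0.1 to 0.4 of one standard error (0.03/0.29 to 0.075/0.19).

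The standard error of the difference in proxy share is √(2q(1 − q)/33), or about 7, 10 and 11 points at q = 10%, 20% and 30%. By the normal approximation, a gap of at least 15 points in either direction then has probability of about 4%, 13% and 18% for a given pair of arms.

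**The case against.** The strongest reply is that randomization takes care of this. Whether a proxy is needed depends on the patient's state on day 1, and allocation is central and concealed, so proxy use is balanced in expectation. Any rater gap becomes part of the within-arm variance that the test already uses, and the type I error stays near nominal. This stands. A reader might infer that a chance imbalance in proxy use makes the arm comparison biased. The article does not support that: chance imbalance is ordinary sampling noise already in the standard error, and step 5 shows it to be well below one standard error under the assumed values. Table 1 places the baseline questionnaires in the allocation column and so leaves their order relative to randomization open, and the day-90 analysis covers survivors only. Either could in principle break the independence, but nothing in the article says that the choice of respondent follows the arm.

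It is also fair to say that a proxy baseline is better than none. Without it the patient would drop out of the complete-case change analysis. A reader might conclude that the score does not measure change at all in these patients; that is too strong, since it measures change with rater error. The objection defends collecting the proxy score, however, and not subtracting it as though the patient had given it.

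Finally, the eCRF and any full analysis plan are not shown. The article does not show that the respondent goes unrecorded, and a missing sensitivity analysis by respondent is no fault here. What the article does fix is the outcome variable and the unadjusted test, and those can be judged. The planned multiple imputation does not help, because a proxy score is observed and not missing.

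**Conclusion.** The point holds as one of measurement and efficiency. For patients with a proxy baseline, the planned HADS and SF-36 change is true change plus a rater gap. The within-arm change is then partly a switch of rater, and the variance of the arm comparison is inflated. The between-arm test remains about valid, provided that proxy use is independent of arm among the patients analysed.

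The size is unknown, because it depends on a proxy share and a rater gap that the article does not give. The figures of 0.02 to 0.20 SD for the within-arm shift and about 4% to 43% for the variance are illustrations under stated assumptions. If only a few patients need a proxy, the effect is small. That the day-90 answers come from patients alone rests on the article naming no proxy there.

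The endpoints are secondary and the primary endpoint is untouched. The change is still worth making, because it costs almost nothing.

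**What to change.** In the paragraph on SF-36, HADS, IES-R and overall assessment, replace the raw difference for HADS and SF-36. Compare the patient-reported day-90 scores between arms by linear regression on randomization group, baseline score, and an indicator of proxy versus patient respondent at baseline. Every outcome value then comes from the same kind of rater, and patients with proxy baselines stay in the analysis. Add the interaction of respondent with baseline score only if there are enough proxy-baseline patients to estimate it; with a handful it would be unstable and should not be mandatory.

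Make sure that the baseline respondent is recorded. Report change from baseline descriptively, only for patients who answered at both times, with the number of proxy baselines in each arm.

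The cost is a change of analysis wording, one data field if the respondent is not already captured, one or two extra model terms beyond the baseline score, and descriptive change scores on fewer patients.

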### Coordination and implementation of the trial

Each medical and paramedical team of the three participating ICUs was trained in the protocol and data collection using the electronic case report form (eCRF) during formal meetings prior to the start of screening and inclusion. The eCRF is developed with CleanWEB™, a centralized, secure, interactive, web-response system accessible from each study center, provided and managed by Telemedicine technologies.

Local physicians and clinical research assistants in each participating ICU are responsible for daily screening and inclusion of patients, compliance with protocol, availability of data requested for the trial, and completion of the eCRF. In accordance with French law, the eCRF and database were validated by appropriate committees (CCTIRS: Comité Consultatif sur le Traitement de l'Information en matière de Recherche dans le domaine de la Santé; CNIL: Commission Nationale de l'Informatique et des Libertés).

## Study endpoints

### Primary endpoint

The primary endpoint is the change in respiratory comfort before the initiation and after 30 minutes of the first NIV session after randomization. The respiratory comfort will be measured using a digital visual scale [14]. This scale is a 10-cm long ruler, shaped like an arrow. It is bounded on the left by “0: no respiratory discomfort” (the smaller base of the arrow) and on the right by “10: maximal respiratory discomfort” (the larger base of the arrow).

The participant marks the level of his/her perception of discomfort directly on the ruler.

### Secondary endpoints

Secondary endpoints are:The evolution of respiratory comfort during the first session of NIV evaluated before initiation, after 5 and 30 minutes, and at 1, 2, 3, 4, 6, 8, 12, 16, 20, 24 hours depending on the length of each NIV session, and at the end of the sessionThe evolution of respiratory comfort evaluated at the same times in each subsequent session, measured using a digital visual scale [14]Changes in respiratory parameters during NIV sessions (respiratory rate, transcutaneous oxygen saturation, exhaled tidal volume) at 5 and 30 minutes and at 1, 2, 3, 4, 6, 8, 12, 16, 20, 24 hours depending on the length of each NIV session and at the end of the sessionChanges in cardiovascular parameters during NIV sessions (heart rate, arterial pressure) at 5 and 30 minutes and at 1, 2, 3, 4, 6, 8, 12, 16, 20, 24 hours depending on the length of each NIV session and at the end of the sessionThe percentage of patients requiring endotracheal intubation (NIV failure) at the end of an NIV sessionThe adequacy of the prescribed NIV session duration and its actual durationThe number of sessions interrupted before the end of the prescribed timeThe percentage of patients requiring physical contention, sedative, or anxiolytic treatments during NIV sessions and ICU stayAnxiety/depression and health-related quality of life evaluated by HADS and SF-36 scores at baseline and after 3 monthsPost-trauma stress induced by NIV, measured with the IES-R scale immediately at discontinuation of NIV session and after 3 months of inclusionThe overall assessment of NIV (in terms of discomfort, satisfaction, and trauma) at the discontinuation of NIV and at day 90.

